#### Analytic strategy

We anticipate that stratification prior to randomization will result in a close matching of T and C groups on demographic and health variables. Prior to statistical analyses, we will use independent samples t-tests (continuous variables) or chi-square tests (categorical variables) to assess the statistical balance between T and C groups on the basis of GA, sex, SES, clinical complications associated with premature birth, and language exposure during treatment and after hospital discharge. Analyses will use an intention-to-treat strategy [57]. If groups are matched on all variables, we will use independent t-tests (two-tailed) to compare T versus C groups on the primary long-term language outcome and the secondary short-term outcomes that relate to white matter development. Should groups not be balanced, and to account for missing data, we will use linear mixed models: T group as a fixed factor and unmatched or missing variables are random factors. Statistical significance is set at *p* < 0.05. Should an imbalance of twins or multiples occurs, we will perform group analyses including all singletons and one randomly selected twin or multiple from each set [58].

We will perform post hoc univariate and/or non-parametric analyses to determine if neural and clinical outcomes are associated with variations in the dose (i.e., number of hours of maternal speech delivered) or length (i.e., number of nights of delivery) of treatment, controlling for GA and PMA. Post hoc covariance analyses will permit further interpretation of either significant or non-significant treatment effects for short- and long-term neural and language outcomes. We will use multiple regression analyses to predict language outcomes from short-term neural and clinical outcomes, while controlling for group status and measures of language exposure.

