### Participants

Preterm neonates born and admitted to the LPCH’s NICU at Stanford University will be eligible to participate. To be eligible, neonates must be born between 24-0/7 and 31-6/7 weeks GA (*N* = 42; T: *n* = 21 and C: *n* = 21). All races and ethnicities will be included. However, we will enroll infants whose family’s primary language is English or Spanish, because of our limitations in communicating with families using other languages. The primary language outcome, the CDI: Words and Gestures Questionnaire, will be administered in English or Spanish, as appropriate [37, 38]. Eligible participants must be free of the following adverse outcomes that could potentially confound language and neuroimaging outcomes: (1) congenital anomalies or recognizable malformation syndromes; (2) serious neurological conditions, including active seizure disorders, history of central nervous system infections or hydrocephalus, intraventricular hemorrhage grades III–IV, and cystic periventricular leukomalacia; (3) surgical treatment for necrotizing enterocolitis; (4) small for GA (< 3 percentile) and/or intra-uterine growth restriction; and (5) major sensori-neural hearing loss.

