#### Randomization and RCT design elements

Eligible participants will be randomized by the principal investigator ([name]), who will not be blinded, in order to provide close monitoring of the procedures. The principal investigator will allocate participants sequentially as they are enrolled to either the T or the C group using the minimization algorithm by Pocock and Simon [41] implemented in the R statistical software package [42]. Randomization will be stratified for (1) GA (24-0/7 to 27-6/7 weeks or 28-0/7 to 31-6/7 weeks), to control for potential development differences in response to the intervention and as a proxy for neural injury, and (2) socioeconomic status (SES) (above versus below average SES; based on Hollingshead Index (HI) [36, 43]), to control for potential differences in language outcomes affected by socioeconomic factors. Taking into account ethical considerations and parental preferences, twins and multiples will be assigned to the same group [44]. Families and research and clinical staff will be blinded to the group status. In the unlikely event that a family, research staff, or clinical staff suspect that an infant may not tolerate the speech recording, the principal investigator will reveal the group assignment.

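### Balance tests choose the primary model: one branch omits the minimisation factors and loses power, the other adjusts in a form that fails for continuous variables

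*Protocol article*

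**What the plan says.** All references are to the protocol article.

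- **Allocation** (Randomization and RCT design elements). Infants are allocated "using the minimization algorithm". The text continues "Randomization will be stratified for (1) GA" in two bands, and names SES, above or below average, as the second factor. SES is included because it may affect language outcomes.
- **Choice of model** (Analytic strategy). Before the outcome analysis, "we will use independent samples t-tests (continuous variables) or chi-square tests (categorical variables) to assess the statistical balance between T and C groups". The variables tested are "GA, sex, SES, clinical complications associated with premature birth, and language exposure during treatment and after hospital discharge".
- **Branch 1.** "If groups are matched on all variables, we will use independent t-tests (two-tailed) to compare T versus C groups", for the primary language outcome and the secondary white matter outcomes.
- **Branch 2.** If groups are not balanced, and to account for missing data, a linear mixed model is used with "T group as a fixed factor and unmatched or missing variables are random factors".
- **Threshold.** "Statistical significance is set at *p* < 0.05".
- **Home language exposure** (Control variables and covariates). Recorded around the 12-month visit, it is to be used as a covariate if the groups differ on it.

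Nowhere are GA and SES placed in the primary model regardless of the balance tests.

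**The concern.** There are three faults in this rule.

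1. In a properly randomised trial, a significant balance test on a baseline variable is a chance event. It is a poor basis for choosing the primary model, and it makes that model unknown until the data are in.
2. Minimisation removes most of the GA and SES variation from the difference between group means. An unadjusted t-test still counts that variation in its standard error, so the test is too cautious if the factors are prognostic.
3. When adjustment is triggered, its form is wrong. A covariate's slope belongs in the fixed part of the model. A random factor treats each distinct value as a separate group.

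In addition, language exposure during treatment and after discharge is measured after randomisation and could itself respond to the intervention. Letting it select the model and enter it can condition away part of the effect under study.

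At stake are power in a trial of 42 infants, and whether the adjusted branch does what it is there to do.

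**Working it through.** **1. The plan's own power figures.** Two-sided two-sample t-test, noncentral t, alpha 0.05:
- 17 per group, d = 1.0: 0.807 (stated 0.8)
- 21 per group, d = 1.0: 0.885 (stated 0.88)
- 21 per group, d = 0.9: 0.812 (stated as above 0.8)

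All three reproduce.

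**2. Branch 1, approximate arithmetic.** Let R² be the share of outcome variance explained by GA and SES. It is assumed, because the protocol gives none. With near-perfect balance on both factors, the true standard error of the difference is about √(1 − R²) times the one the t-test uses. The critical value of 2.021 (40 df) then acts like 2.021/√(1 − R²):
- R² = 0.1: 2.021/0.949 = 2.13, size about 0.039
- R² = 0.2: 2.021/0.894 = 2.26, size about 0.029
- R² = 0.3: 2.021/0.837 = 2.42, size about 0.020

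**3. Branch 1, simulation.** Assumptions: 42 independent infants, two binary factors with equally common levels, minimisation with a 0.8 biased coin, and d in units of the total SD.

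| R² | Size, t-test | Power at d = 0.9, t-test | Power at d = 0.9, GA and SES as fixed effects |
|---|---|---|---|
| 0 | 0.053 | 0.80 | 0.80 |
| 0.1 | 0.035 | 0.82 | 0.85 |
| 0.2 | 0.031 | 0.83 | 0.88 |
| 0.3 | 0.024 | 0.83 | 0.92 |

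The adjusted model keeps its size near 0.05 throughout. Repeat simulations moved the t-test sizes by up to about 0.006 and the powers by up to about 0.02, without changing the pattern.

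**4. How often branch 2 is entered by chance.** The protocol names categories of variables, so the number of tests must be assumed. Take eight, including GA and SES. Those two are minimised and are flagged in about 0.5% of trials or fewer, which leaves six free tests: 1 − 0.95⁶ = 0.265. Simulation gives about 26 to 28%. The rate falls if the tests are correlated: about 16% in a run where the other variables correlated 0.6 with GA (assumed).

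**5. What branch 2 does.** Take a covariate with a 0.65 SD imbalance and an outcome slope of 0.5. The unadjusted bias is 0.65 × 0.5 = 0.325.
- Continuous covariate, all values distinct: as a random factor, each value is its own level and merges with the residual. The bias stays at 0.33, against 0.01 with a fixed slope.
- Binary covariate: as a two-level random factor, the bias falls from 0.34 to 0.03, against 0.00 as a fixed effect. The variance component rests on two levels, and some fits did not converge.

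**6. Consistency of the text.** Control variables and covariates makes home language exposure a covariate when groups differ on it. Analytic strategy would make the same variable a random factor.

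**The case against.** The best defence is that error control is safe and the loss modest. The t-test branch is conservative, and the two-stage rule as a whole had size 3.4 to 4.4% when simulated with fixed-effect adjustment on triggering. Its power of 0.80 to 0.83 at d = 0.9 is about what the protocol promises. The gain from adjustment depends on an R² that the documents do not give and vanishes at R² = 0. The term random factors may be loose wording for covariates, as the covariates section suggests. All of this stands, and it limits the point to efficiency, form of adjustment and pre-specification.

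Several stronger readings are tempting but not supported:
- **False positives are inflated.** The simulations show the opposite.
- **Eight to ten tests give a 34 to 40% chance of switching.** That is 1 − 0.95⁸ to 1 − 0.95¹⁰. It treats GA and SES as free to differ when they are minimised, and all tests as independent.
- **The balance tests have low power against a true imbalance.** After randomisation there is no population imbalance to detect; only the realised one matters.
- **The estimand depends on p-values.** For baseline covariates in a linear model, adjustment changes precision, not the quantity estimated. Only the post-randomisation exposure variables raise that question.
- **Branch 2 never removes imbalance.** Binary variables are mostly adjusted for.
- **Infants without an 18-month CDI are lost.** The protocol says mixed models will account for missing data and does not say how. The detail may sit in an analysis plan not shown.

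**Conclusion.** The rule as written should be replaced. In the t-test branch it gives up about 3 points of power at R² = 0.1 (0.82 against 0.85) and about 9 at R² = 0.3 (0.83 against 0.92), and nothing at R² = 0. In the mixed-model branch, read literally, it makes no adjustment for a continuous variable and a fragile one for a binary variable, and it contradicts the protocol's own covariates section. That branch would be reached in about a quarter of sound randomisations under the eight-test assumption, and less often with correlated tests. The use of post-randomisation language exposure as a trigger and model term is a separate fault that does not depend on any of these figures.

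The sizes rest on the assumed R², the 0.8 coin, equally common factor levels and independent infants; multiples were not modelled. The protocol's power calculation is correct for the test it describes.

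**What to change.** - Delete the balance-test rule. Pre-specify one linear model for every T versus C comparison, with treatment, GA and SES as fixed effects.
- Keep language exposure during treatment and after discharge out of the primary model; use it in secondary analyses.
- Reconcile Control variables and covariates with Analytic strategy, so that adjustment variables are described the same way in both.
- Optional, for missing 18-month CDI scores: model the 12- and 18-month scores, both already planned, jointly with a random effect for infant, and report the 18-month contrast as primary.

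The cost is wording and two degrees of freedom (38 instead of 40 with 42 infants and two binary factors). GA and SES are already collected. At R² = 0 the simulated power is unchanged at 0.80.

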Our aim is to establish whether a language intervention (treatment) administered in the NICU has the potential to promote healthy language and brain development in very preterm infants. To achieve this goal, we have designed an interventional randomized controlled trial (RCT) that will test the causal effect of increased exposure to maternal speech in the NICU on language outcomes and white matter development in infants born very preterm. Our first aim will assess the long-term effects of increased maternal speech exposure on an infant’s expressive and receptive language abilities measured at 12–18 months of age adjusted for prematurity (AA). We focus on these language abilities because they have been linked to language processing abilities that are known to be strong predictors of later academic outcomes [34–36]. We hypothesize that, compared to controls, infants in the treatment group will demonstrate more advanced language skills at 12–18 months AA. Our second aim will assess the effects of increased maternal speech exposure on an infant’s white matter development at ~ 36 weeks PMA and 12 months AA. Measuring white matter development at these two ages will allow us to assess whether possible immediate effects of increased maternal speech exposure on white matter development are sustained over the first year of life. We hypothesize that, compared to controls, infants in the treatment group will demonstrate changes in dMRI measures reflecting increased white matter development. Specifically, infants in the treatment group will demonstrate lower MD.

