### Outcome assessment methods

The primary outcome is language development (domain) assessed through the MacArthur-Bates CDI (measure) at (metric) 18 months AA (time point), quantified as expressive and receptive language raw scores and aggregated as group means (aggregation). The secondary outcome is white matter development (domain) assessed through dMRI scans (measure) collected at (metric) two different time points (time point): (1) prior to hospital discharge (neonatal time point) and (2) at 12 months AA (1-year time point), quantified with the dMRI metric (MD) and aggregated as group means (aggregation).

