### Analysis plan

#### Power calculations

We calculated the sample size based on power. The significance level is *p* < 0.05 for all analyses. Power estimates are based on the means, standard deviations, and samples size from an RCT neuroimaging study of preterm neonates that showed a significant effect of a parent-based NICU intervention on diffusion metrics measured at close-to-term age (Cohen’s *d* = 1.03) and developmental outcomes (Cohen’s *d* = 1.77) measured at 9 months AA [56]. Thus, if we assume an effect size that is more conservative than this earlier study, specifically Cohen’s *d* = 1.0, we will have a power of ß = 0.8, if we enroll a sample size of at least 17 participants per group. Therefore, our planned enrollment of 21 participants per group will yield a power of ß = 0.88 to detect an effect size at that level (Cohen’s *d* = 1.0). If our effect size is even smaller than we anticipate, for example, Cohen’s *d* = 0.9, a planned enrollment of 21 per group will still yield a power greater than 0.8 to detect a treatment effect.

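### The specified arm comparison names only short-term white matter outcomes, although mean diffusivity at 12 months is a secondary endpoint, and no analysis of persistence is stated

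*Protocol article*

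**What the plan says.** Three parts of the protocol article bear on this.

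- **Outcome assessment methods** defines the secondary outcome as MD at two time points, "1) prior to hospital discharge (neonatal time point) and (2) at 12 months AA (1-year time point"), each summarised by group means. MD at the later scan is therefore as much a part of the secondary endpoint as MD at the earlier one.
- **Background** (second aim) explains why there are two scans: to "assess whether possible immediate effects of increased maternal speech exposure on white matter development are sustained over the first year of life". The Abstract's Methods paragraph also gives the effect on structural connectivity at 12 months as something the trial assesses.
- **Analytic strategy** says "we will use independent t-tests (two-tailed) to compare T versus C groups" if the groups are matched, and lists the outcomes as the long-term language measure and "the secondary short-term outcomes that relate to white matter development". If groups are unbalanced or data are missing, a linear mixed model is used, with group as a fixed factor. No age term and no group-by-age term is given.

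Long-term neural effects appear once more in Analytic strategy: "Post hoc covariance analyses will permit further interpretation of either significant or non-significant treatment effects for short- and long-term neural and language outcomes".

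**The concern.** The specified test and the endpoint definition do not cover the same outcomes. Read literally, the arm comparison for white matter stops at the neonatal scan, and the 12-month scan has no stated comparison of its own.

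Nor is it stated how a sustained effect would be recognised. The second aim concerns two ages taken together, so it needs at least a 12-month contrast and a rule for drawing a conclusion about persistence from it. If that is left open, the choice may be made after the data are seen. One easy choice, reading a significant early result followed by a non-significant later one as fading, is unreliable in a trial of this size.

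**Working it through.** **1. Which outcomes the specified test covers**

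| Place | Neonatal MD | 12-month MD |
|---|---|---|
| Outcome assessment methods | secondary outcome | secondary outcome |
| Background, second aim | immediate effect | sustained effect |
| Analytic strategy, arm comparison | named (short-term) | not named |
| Analytic strategy, post hoc sentence | effect presupposed | effect presupposed |

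The label short-term is not a loose name for both scans. The test sentence sets long-term language against short-term white matter, and the next paragraph separates short- from long-term for neural and language outcomes alike. The closing regression in that paragraph uses only short-term neural outcomes as predictors, so it does not fill the gap.

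**2. The plan's own power figures**

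Inputs from Power calculations: two-sided 0.05, d = 1.0 or 0.9, 21 per group. With a two-sample t-test (noncentral t):

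- d = 1.0: required n is 16.7, so 17 per group (power 0.807).
- 21 per group: power 0.885 at d = 1.0 (stated 0.88) and 0.812 at d = 0.9 (stated above 0.8).

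These figures reproduce. A 12-month t-test with all 21 per group would have the same power for the same d. The diffusion effect size behind the plan (d = 1.03) was measured close to term age, so it does not directly support power at 12 months.

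**3. What an arm-by-age term could show**

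Assumptions, none of them given in the document: equal SD of MD at both ages (set to 1), correlation r between scans of 0.3 to 0.5, 21 complete pairs per arm, and a fade from d = 1.0 to d = 0.5. The interaction is a two-sample comparison of within-infant change:

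- SD of change = √(2(1 − r)), which is 1.183 at r = 0.3 and 1.000 at r = 0.5.
- Standardised difference = 0.5 / SD of change, which is 0.423 and 0.500.
- Power at two-sided 0.05 = 0.27 and 0.35. With 15 pairs per arm it is 0.20 and 0.26.

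A non-significant interaction would therefore say little about persistence.

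**4. What comparing two p-values would show**

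I simulated equal true effects at both ages, r = 0.3 to 0.5, with a t-test at each age. The pattern of significance at the neonatal scan and non-significance at 12 months then arises, with no fading at all, in:

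| Scanned per arm at 12 months | d = 0.8 | d = 1.0 |
|---|---|---|
| 21 | 14–17% | 8–9% |
| 15 (assumption) | 26–28% | 19–20% |

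**5. Precision of the 12-month contrast**

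With 21 per arm, the half-width of the 95% CI is about t(0.975; 40 df) × √(2/21) = 2.021 × 0.309 = 0.62 SD. This is wide, but it addresses directly whether an arm difference remains at 12 months.

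**The case against.** The strongest reply is that the 12-month comparison is evidently planned and one sentence is merely worded too narrowly. Effects can be called significant or non-significant only if they are tested, and the post hoc sentence speaks of long-term neural effects in those terms. The outcome definition provides for group means at both scans. This stands. A reader might infer that no treatment test of 12-month MD is planned at all, but the text does not support that.

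A reader might also infer that infants without a 12-month scan would simply be dropped. Analytic strategy names linear mixed models to account for missing data, so a complete-case t-test is not the stated plan when scans are missing.

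Nor does the protocol say that it will judge persistence by comparing p-values. The percentages in step 4 describe a hazard that the open wording leaves room for, not an error that the plan commits. On one plain reading, sustained means only that an arm difference is present at 12 months, and then the 12-month contrast suffices.

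Finally, an article may leave model detail to a full protocol or analysis plan that is not shown. That is fair for covariance structure and similar matters. It does not remove a conflict between two statements that the article itself makes about which outcomes are compared.

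**Conclusion.** The point holds as an inconsistency within the protocol article. The specified arm comparison omits a time point that the outcome definition, the second aim and the Abstract all include, and no analysis of persistence is stated. A 12-month comparison is presupposed but not specified.

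It concerns a secondary endpoint. The primary language analysis and the sample size are unaffected, and the plan's power figures reproduce.

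The textual conflict rests on no assumption. The interaction power of 0.27 to 0.35 rests on equal SDs, correlation 0.3 to 0.5 and 21 complete pairs per arm. The misleading-pattern rates rest on the same correlations and equal standardised effects at both ages, and the higher ones also on an assumed 15 per arm at 12 months. If the SD of MD differs between ages, an arm-by-age term on raw MD tests equal absolute differences, which is not the same as equal standardised effects.

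**What to change.** Reword Analytic strategy so that the secondary comparison covers MD at both the neonatal scan and 12 months adjusted age:

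- Analyse both scans in one linear mixed model with arm, age and arm-by-age, plus the stratification factors (GA and SES), including all randomised infants with at least one scan.
- Report the arm difference with its 95% CI at each age. The 12-month difference is the long-term secondary test and carries the conclusion on persistence.
- Report the arm-by-age estimate with its CI as supportive only, because of its low power.
- State that fading will not be inferred from one significant and one non-significant p-value.

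The cost is a change of wording and slightly more analysis work. No new data are needed.

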**Methods:**

This randomized controlled trial assesses the long-term effects of increased maternal speech exposure on structural connectivity at 12 months of age (age adjusted for prematurity (AA)) and language outcomes between 12 and 18 months of age AA. Study participants (*N* = 42) will include infants born very preterm (24–31 weeks 6/7 days GA). Newborns are randomly assigned to the treatment (*n* = 21) or standard medical care (*n* = 21) group. Treatment consists of increased maternal speech exposure, accomplished by playing audio recordings of each baby’s own mother reading a children’s book via an iPod placed in their crib/incubator. Infants in the control group have the identical iPod setup but are not played recordings. The primary outcome will be measures of expressive and receptive language skills, obtained from a parent questionnaire collected at 12–18 months AA. The secondary outcome will be measures of white matter development, including the mean diffusivity and fractional anisotropy derived from diffusion magnetic resonance imaging scans performed at around 36 weeks postmenstrual age during the infants’ routine brain imaging session before hospital discharge and 12 months AA.

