## Methods

### Study design

To achieve these aims, we propose an RCT that will involve 42 very preterm infants born and cared for at Stanford’s Lucile Packard Children’s Hospital (LPCH). Enrollment is planned from November 2019 to December 2021. For infants who meet the inclusion criteria of gestational age at birth (GA) of 24-0/7 to 31-6/7 weeks, we will obtain informed consent and questionnaires about the family’s demographics and language from parents, and a speech recording from each mother. Infants will then be randomized to the treatment (T) or control (C) group. Infants randomized to either T or C group will receive standard medical care, with the exception that infants randomized to the T group will also receive the maternal speech intervention achieved by playing recordings of maternal voice via iPods placed in an infant’s incubator or open crib. Infants in the C group will have the same auditory setup to ensure that parents and clinical staff remain blinded to the group status. The duration of the intervention will begin once an infant gets transferred to the intermediate care nursery, indicating medical stability, and end once an infant has received their clinical MRI, which is part of the standard medical care at LPCH and is performed prior to hospital discharge (~ 36–38 weeks PMA). The long-term effects of the intervention will be assessed at 12 months and 18 months AA. At 12 months AA, infant participants will undergo a dMRI scan during natural sleep, and parents will complete the MacArthur-Bates Communicative Development Inventories (CDI): Words and Gestures Questionnaire [37]. At 18 months AA, parents will complete another CDI: Words and Gestures Questionnaire, the primary outcome assessment of language development (see Fig. 1).

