### Primary outcome: language development

#### MacArthur-Bates CDI

In order to measure language development and production, parents of infant participants will complete the CDI: Words and Gestures Questionnaire [46] at 12 months AA and 18 months AA via web form or mail form with guidance from a trained clinical research assistant. The CDI Words and Gestures Questionnaire is a parent checklist that evaluates both verbal and non-verbal communication, as well as some aspects of play. Split into two parts, “The Early Words” section examines infants’ intentional linguistic communication, understanding, vocabulary, and language-based social interactions, while the “Actions and Gestures” section gauges communicative gestures, play, and symbolic understanding. As these metrics of language development are related to measures of processing speed and predictive of later language outcomes, the CDI Words and Gestures Questionnaire will serve as our primary measure of language development.

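### The stated missing-data model has one 18-month CDI score per infant, so it recovers no missing primary outcome, and no stated analysis uses the planned 12-month CDI

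*Protocol article*

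**What the plan says.** All references are to the protocol article.

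- **Primary outcome.** Outcome assessment methods defines language development as "assessed through the MacArthur-Bates CDI (measure) at (metric) 18 months AA (time point", quantified by expressive and receptive raw scores. Study design agrees: "At 18 months AA, parents will complete another CDI: Words and Gestures Questionnaire, the primary outcome assessment of language development".
- **A wider window elsewhere.** The Methods paragraph of the abstract describes the primary outcome as "obtained from a parent questionnaire collected at 12–18 months AA". The first aim, in the Background, uses the same window.
- **Two CDI visits.** The MacArthur-Bates CDI section plans that "parents of infant participants will complete the CDI: Words and Gestures Questionnaire [46] at 12 months AA and 18 months AA".
- **Analysis.** Analytic strategy states "Analyses will use an intention-to-treat strategy [57". If the groups match on all variables, they are compared by two-sided t-test. If they do not, and for missing data, the plan is: "to account for missing data, we will use linear mixed models: T group as a fixed factor and unmatched or missing variables are random factors". It mentions no visit term, no repeated response and no 12-month score.
- **Loss to follow-up.** No rate is stated. The article has a retention plan, so some loss is foreseen.

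**The concern.** A likelihood-based mixed model uses an infant whose outcome is missing only when another measurement of the same infant is part of the response. With one 18-month score per infant there is no such measurement, and the infant contributes nothing. Declaring an incomplete variable a random factor gives it a variance component but does not supply the absent values. The sentence thus claims to account for missing data and, for the primary outcome, does not.

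Three things are at stake:
- The comparison is restricted to completers while the text claims intention to treat.
- The power statement assumes that every enrolled infant yields an 18-month score.
- If families leave in a way related to the infant's earlier language, the completer difference can be biased, although the same questionnaire at 12 months would carry information about those infants.

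Follow-up is long. From the pre-discharge scan at 36–38 weeks PMA to term is 2–4 weeks, so 18 months adjusted age falls roughly 18.5–19 months after the scan.

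**Working it through.** **Inputs from the article:** 21 infants per arm, two-sided alpha 0.05, d = 1.0 and d = 0.9 (Power calculations and Analytic strategy).

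**Assumed, because the article does not give them:** fraction q lost at 18 months (20% or 30%), correlation ρ between 12- and 18-month CDI (0.5 to 0.7), and a 12-month CDI present for every infant.

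**1. The plan's own figures.** Power of the two-sample t-test from the noncentral t distribution:

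| n per arm | d | Power | Article |
|---|---|---|---|
| 17 | 1.0 | 0.807 | 0.8 |
| 21 | 1.0 | 0.885 | 0.88 |
| 21 | 0.9 | 0.812 | above 0.8 |

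All three reproduce, but only with an 18-month score from every infant. With 20 per arm, power at d = 0.9 is 0.792, so losing one infant per arm already falls below the stated 0.8.

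**2. Who is in the model.** In an example data set of 42 infants with 8 missing 18-month scores, a mixed model on the 18-month score used 34 infants. A two-visit model on the same data used all 42 (34 + 42 = 76 rows).

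**3. Precision.** If loss at 18 months is unrelated to the scores, completers give n(1 − q) per arm. With both visits in the response, the variance of an arm's 18-month mean is (σ²/n) × [ρ² + (1 − ρ²)/(1 − q)], so effective n = 21 / [ρ² + (1 − ρ²)/(1 − q)].

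- q = 0.2: completers 21 × 0.8 = 16.8.
  - ρ = 0.5: 0.25 + 0.75/0.8 = 1.1875; 21/1.1875 = 17.7.
  - ρ = 0.7: 0.49 + 0.51/0.8 = 1.1275; 21/1.1275 = 18.6.
- q = 0.3: completers 21 × 0.7 = 14.7.
  - ρ = 0.5: 0.25 + 0.75/0.7 = 1.3214; 21/1.3214 = 15.9.
  - ρ = 0.7: 0.49 + 0.51/0.7 = 1.2186; 21/1.2186 = 17.2.

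| Loss | Completers: n, power at d = 1.0 | Two visits: effective n, power at d = 1.0 |
|---|---|---|
| 20% | 16.8, 0.80 | 17.7–18.6, 0.82–0.84 |
| 30% | 14.7, 0.74 | 15.9–17.2, 0.78–0.81 |

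Share of the lost effective n that is recovered, before rounding:
- At 20% loss, 4.2 per arm are lost. (17.68 − 16.8)/4.2 = 21% and (18.63 − 16.8)/4.2 = 43%.
- At 30% loss, 6.3 are lost. (15.89 − 14.7)/6.3 = 19% and (17.23 − 14.7)/6.3 = 40%.

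The formula is a large-sample one and ignores the cost of estimating the extra variance parameters.

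**4. Bias.** Large-sample simulations with true d = 1.0 at 18 months and loss that depends on the 12-month score:
- Low 12-month scorers lost at 40% and high scorers at 0%: the completer effect is attenuated by 1–3%.
- An arm-specific cut-off with equal loss by arm: about zero.
- A steep logistic dependence (slope 1.5 per SD), 20–30% loss, ρ 0.5–0.7: attenuation of 5–8% if the 12-month effect is d = 0.5, and 9–16% if it is d = 1.0.

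With d = 1.0 at 12 months and 20% overall loss, the steep case implies about 29% loss in control and 11% in treatment. Adjusting for the 12-month score returned the estimate to about 1.00.

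**The case against.** - **The single response is inferred.** Analytic strategy refers only to the long-term language outcome, and the abstract and first aim give a 12–18 month window. This stands as a limit. Study design and Outcome assessment methods nevertheless both name 18 months, and the model as written has no visit term that could accommodate two scores. The time point needs reconciling first.
- **The clause may concern covariates.** It pairs unmatched with missing variables, so it may be a rule for incomplete balance variables, with missing outcomes left to an unseen analysis plan. That reading is possible. But the sentence offers the model as the answer to missing data without restriction, and a random factor does not handle a missing covariate either.
- **Using both visits does not deliver full intention to treat.** A reader might infer that the 12-month CDI will exist for every infant. The article plans it for all and cannot assure it; families lost before 12 months have neither score and stay outside the model.
- **The gain is small.** A reader might take ρ² (25–49%) as the share of lost information recovered. It is the share of excess variance removed; the recovered effective n is 19–43% of what was lost. At low loss or low correlation the gain nearly vanishes.
- **Serious bias is not shown.** A reader might conclude that the completer comparison is badly biased. The larger attenuation needs steep dropout with clearly unequal loss between arms. In the scenarios examined, any bias was toward the null.

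**Conclusion.** The point holds in a limited form. With the primary CDI at 18 months, the stated mixed model recovers no missing primary outcome under any assumption about dropout or correlation, and the comparison is a completer analysis beside an intention-to-treat claim. This is a stated rule that does not do what it says, not a detail left to another document.

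The numerical benefit of correcting it is modest: about two to four percentage points of power at 20% loss and d = 1.0, and about three to seven at 30%. Those figures depend on the assumed correlation of 0.5–0.7, the assumed loss and a complete 12-month CDI. Completer bias ranges from near zero to about 16% attenuation, depending on a dropout pattern the article gives no means of predicting. The documents do not support saying that the trial's result would be invalid or seriously biased. The change is worth making because it is cheap and makes the missing-data statement true for infants with a 12-month score.

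**What to change.** In Analytic strategy:

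1. Confirm 18 months adjusted age as the primary time point, and bring the 12–18 month window in the abstract and first aim into line with it.
2. Delete the clause that makes unmatched or missing variables random factors.
3. For each CDI score, fit a repeated-measures mixed model to the 12- and 18-month values with arm, visit, arm-by-visit and an unstructured within-infant covariance. The 18-month arm difference is the primary contrast, and every randomised infant with at least one CDI is included.
4. The deleted clause also carried the plan's only mixed-model adjustment for imbalance. Keep covariate adjustment by entering the stratification factors, GA and SES, as fixed effects. Account for multiples from one family, who are assigned together. Say how this model relates to the t-test.
5. State that infants with neither CDI are not recovered, and qualify the intention-to-treat sentence accordingly.

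Multiple imputation using the 12-month CDI is a reasonable alternative to step 3.

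The cost is wording only, with no new data or visits. The downside is a few more variance parameters to estimate in a trial of 42 infants. With complete data and no covariates, the 18-month contrast remains the simple difference in means.
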